## **11.3 Benefits to the community**

If shown to be effective, this would contribute to reducing morbidity and mortality amongst the children in the community. Based on the positive outcome of this study, MSF will adapt protocols to include provision of nutritional supplementation for children with serious acute illness. Assuming positive benefit of the intervention, MSF will advocate with the MoH, and with donors for provision of the supplement. While it is accepted that RUTF is an expensive intervention and may be difficult for the MoH to implement alone, previous MSF prevention studies for malnutrition have resulted in uptake of the RUTF distribution strategy by UNICEF and WFP. If the study shows MNP to be effective, we anticipate this to be an intervention that can be implemented with minimal cost impact. In addition, we would consider cost effectiveness studies if this was needed to convince decision-makers to implement the nutritional intervention.

The study also hopes to contribute to an improved understanding within the community, including medical staff, that good nutrition is essential after during and an acute infection.

Study participants will further benefit from monthly routine screening, intensified follow-up treatment and care.

Finally we want to address the issue of commercial interest. Plumpynut® is under patent protection currently. The Access to Medicines Campaign of MSF has been actively following this issue for the last years, and currently the patent is under pressure in a number of countries. More manufacturers are now producing RUTF, for example Compact produces a nutritionally equivalent product, called EeZeePaste® which is now used in some MSF programs. MixMe® is a product that as stated is widely used and similarly to another product on the market. It is

distributed by UNICEF through a donation from the manufacturing company. We therefore do not see any direct commercial interest accruing as a result of this study to either the makers of Plumpynut® or MixMe®.

#### **11.4 Feedback of results**

Individual child results will be shared and discussed with the guardian in such a manner to not jeopardize established blinding of the study interventions. At the end of the study, feedback and preliminary outcomes will be provided to the community and to medical authorities.

#### **11.5 Potential risks**

The potential risk due to a nutritional supplementation is very low. The supplementation products have a history of proven effectiveness and benefit in similar settings. Nonetheless, any intervention carries with it a certain level of risk and, as such, participants must be monitored closely.

A paper by Caulfield *et al.* [30] reviewed the relation between iron supplementation and risk of reduced malaria parasite clearance rates and increased risk of treatment failure. However, these studies have been criticised on several points, including the use of a malaria treatment (sulfadoxine - pyrimethamine) in an area with parasite resistance to these drug components. [31]

Caulfield *et al.* conclude that no consensus exists on the risks of malaria morbidity and mortality associated with iron supplementation and that the alleviation of anaemia through iron supplementation is likely to have a far greater net benefit for an iron-deficient population, including those in malaria-endemic regions. The WHO concludes that routine iron supplementation is prioritised even in malaria endemic regions. [32] A recent Cochrane review (2009) that includes the studies mentioned above in their review, concludes that iron does not increase the risk of clinical malaria or death, when regular malaria surveillance and treatment services are provided.[33]

#### **11.6 Adverse events**

An **adverse event** (AE) is any medical event affecting a clinical trial participant.

For each adverse event should be evaluated whether this event is potentially directly related to the RUTF or MNP supplementation, e.g. vomiting, rash, sudden death after eating etc.; An **adverse reaction** (AR) is where it is suspected that an adverse event has been caused by a reaction to one of the supplements.

In this study the primary (incidence of malnutrition) and several secondary outcomes (e.g. frequency of disease) are per definition an adverse event but these will not be considered as an adverse reaction.

A serious adverse event /reaction

- results in death;
- is life threatening (i.e. the subject was at risk of death at the time of the event; it does not refer to an event which hypothetically might have caused death if it were more severe);
- requires hospitalisation; (excluding a therapeutic feeding centre)
- results in persistent or significant disability or incapacity;

Participants will be instructed to contact the clinic if any medical condition develops. The study team will examine the patient and will contact the FRC when a serious adverse event or a suspected adverse reaction (serious or not) occurred. The FRC will report the information to the PI within 24–48 hours of becoming aware of the event. The FRC will initiate the appropriate care and treatment according to their medical judgment.

The report includes study group, type of event, onset date, investigator assessment of severity and causality, date of resolution as well as treatment required, investigations needed and outcome.(see annex F8-serious adverse event/reaction). Depending on severity, when an SAE / SAR occurs, the FRC will review all documentation (e.g. hospital notes, laboratory and diagnostic reports) related to the event. Alternative causes such as natural history of the underlying disease, concomitant therapy, other risk factors and the temporal relationship of the event to the supplementation will be considered.

A subgroup of the study advisory group (including the OCBA Medical Director, the Principal Investigator) will continuously review the occurrence of all serious adverse events and adverse reactions. On authority of the OCBA Medical Director or MoH of Karamoja the study can be interrupted altered or stopped as a result the investigation of adverse reactions (SAE or SAR).

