## **6.2 Blinding**

Owing to the nature of the product packaging and use of a control group without placebo study participants will not be blinded to which study group they were assigned. It will also not be possible to blind staff distributing the supplement.

Study staff blinded to the allocation treatment includes:

- Principle investigator
- Co-investigators
- Field Research Coordinator
- All clinical and ancillary medical staff
- Technical staff collecting anthropometric measurements
- Questionnaire interviewers
- Data managers
- Statisticians

Every effort will be made to ensure that study staff remains blinded to the treatment allocation. Efforts will be made to inform participants and staff to avoid discussion that might reveal allocation.

The allocation scheme will be formally revealed only after the data from the last participant has been captured.

Each participant will be assigned a unique study identification number, used to identify the study participant in all procedures. Study numbers will be assigned sequentially as subjects enter the study. Once a number has been assigned, that number will not be used again (e.g. if a subject discontinues or a number is allocated incorrectly).

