## **6.3 Treatment allocation**

The study dispenser\* will have access to a register with all unique study numbers and the assigned intervention. The study dispenser will allocate the study group to the participant when the participant collects the nutritional supplement. As such, the dispenser will be the only person of the study team to know the allocation scheme. The allocation register will be kept by the dispenser in such a manner that guarantees no unauthorized staff can have access. (see annex f9-dispensary allocation register)

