#### 8.3.1 Weight

**Time of day:** Because the weight of an individual varies during the day, weight will be measured at the same time of day on each follow up visit. With patients being recruited throughout the day, enrolment in the study and the first weight measured will be at any time on day-0.

To limit intra-day variation in weight, efforts will be made to ensure follow-up visits are scheduled at the same time of the day throughout the 6 month study follow-up. A weighing within 3 hours on either side of the original weighing will be accepted. If a patient arrives outside this limit, the participant will be asked to return the next day within the proper time window.

**Weighing procedures:** Two weighing scales, both SECA model 835, a very precise electronic scale, will be used for small babies and toddlers sitting or standing on the scale. Below weights of 20 kg the scale has a precision of +/-20 grams and for heavier weights up to 50 kg a precision of +/-50 grams. To minimize inaccuracy due to a child's movement, great care will be taken to place the scale level and on a stable surface and every effort will be made to ensure that restless children are kept calm during the weighing procedure. Quality control measures will be taken to ensure scale accuracy and the scales will be checked daily by a constant weight of 10Kg.

The weighing will be done by the same team of two (three) persons throughout the study, monitored and supervised closely by the field research coordinator (FRC). All children will be weighed undressed and without jewellery or other ornaments. One person will perform the weighing (ensuring scale is correctly positioned, correctly calibrated, and assisting the guardian with placing the child on the scale). The weight will be taken when the child is relatively still. This same person will read out loud the weight measured. The second person will visually observe the weight on the digital scale to confirm that it has been correctly read out loud and the second person will verbally repeat the weight and record the confirmed result on the appropriate form.

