## **8.6 Emergency unblinding procedures**

Only when a serious adverse event occurs and it is deemed necessary to unblind a patient's intervention group will that patient's allocation be revealed.

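### Section 11.6 puts the study group on every serious event and suspected reaction report passed between two roles that section 6.2 lists as blinded

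*Protocol*

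**What the plan says.** Four sections of the protocol bear on who may learn a child's arm.

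- **Section 6.2 (Blinding)** opens a list with "Study staff blinded to the allocation treatment includes" and names, among others, the principal investigator, the co-investigators, the "Field Research Coordinator", all clinical staff, the anthropometry staff and the statisticians. It commits to keeping these people blinded and places the formal release of the allocation after the last participant's data are in.
- **Section 6.3 (Treatment allocation)** says that "the dispenser will be the only person of the study team to know the allocation scheme".
- **Section 8.6 (Emergency unblinding)** sets the exception. It begins "Only when a serious adverse event occurs and it is deemed necessary to unblind" and covers that one patient's allocation.
- **Section 11.6 (Adverse events)** sets the reporting route. The study team "will contact the FRC when a serious adverse event or a suspected adverse reaction (serious or not) occurred". Then, "The FRC will report the information to the PI within 24–48 hours of becoming aware of the event". The content follows: "The report includes study group, type of event, onset date, investigator assessment of severity and causality".

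Section 11.7 adds that the principal investigator and the coordinator both belong to the subgroup that continuously reviews serious adverse events and reactions. Section 8.3.1 makes the coordinator the close supervisor of the weighing team, and section 10.1 gives the same role regular evaluation of clinical procedures and data collection.

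**The concern.** Guardians and the dispenser know the arm by design, because the products are recognisable and there is no placebo. The staff blind is therefore the only blind this trial has, and it is what protects measurement and judgement. Section 11.6 opens it through an ordinary administrative step, with no decision that unblinding is needed.

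Two things are at stake. The first is causality. Section 11.6 defines an adverse reaction as an event suspected to be caused by one of the supplements, so a control child cannot have one. Once the arm stands on the report, it can settle the causality question for a control child and colour it for a supplemented child. The second is oversight of measurement. Weight feeds the weight-for-height index and so the primary endpoint, and the person supervising the weighing would know the arm of each reported child who stays in follow-up.

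**Working it through.** No arithmetic applies. The check is whether one set of actions can satisfy all four sections.

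**Step 1: who handles the report.** Under 11.6 the study team alerts the coordinator, and the coordinator reports to the principal investigator. Both are on the 6.2 list.

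**Step 2: where the study group would come from.** Under 6.3 only the dispenser has it. To complete the field, someone must obtain it from the dispenser. Section 11.6 describes no sealed, coded or separate route past the coordinator or the principal investigator.

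**Step 3: compare the rules for each kind of reported event.**

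| Reported event | 8.6: may the allocation be revealed? | 11.6: is the study group on the report? | Compatible? |
|---|---|---|---|
| Serious adverse event, unblinding judged necessary | Yes | Yes | Yes |
| Serious adverse event, unblinding not judged necessary | No | Yes | No |
| Suspected adverse reaction, not serious | No, since 8.6 requires a serious event | Yes, since the text draws no distinction | No |

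Only the first row can be carried out without breaking another section. Section 8.6 cannot be read as cover for 11.6, because it calls for a judgement about one patient, while 11.6 lists the study group alongside event type and onset date as standard content.

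**Step 4: how far the unblinding reaches.** It is per child. Randomisation is simple (6.1), so learning one child's arm says next to nothing about the next child's. The allocation register stays with the dispenser, and the rest of the list stays concealed.

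**Step 5: what the arm sits beside.** The same sentence of 11.6 lists the study group and the assessment of severity and causality. The text does not say which is completed first, so nothing ensures that the assessment precedes knowledge of the arm.

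**The case against.** The strongest case on the other side has several parts.

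- **The consequence is modest.** Guardians and the dispenser are unblinded anyway. The coordinator supervises but does not weigh: two other staff read and confirm a digital scale. Children who die contribute no later weights. This stands, and it limits the likely effect on the primary endpoint. It does not remove the contradiction.
- **The form may mask the arm.** Annex F8 is not shown, and its title mentions only serious events and reactions, so non-serious reactions may not go on that form. This cannot be excluded. But 11.6 itself states the report's content, mentions no masking, and does not separate serious from non-serious reports.
- **A suspected reaction hints at an active arm in any case.** True. Removing the field does not make causality fully blind, but it stops the arm from being handed over as a matter of routine.

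Three stronger readings are tempting and should not be drawn.

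- A reader might infer **an unplanned interim look by arm**. Section 11.7 openly plans continuous safety review. Its statement that no interim analysis is required is argued from the primary outcome, and 11.6 says malnutrition will not count as an adverse reaction and leaves therapeutic feeding admissions out of the hospitalisation criterion. Neither section describes totals by arm.
- A reader might **size the problem from the under-five mortality rate in section 1.1**. That rate comes from a general survey in Nigeria, whereas this trial excludes acutely malnourished and severely ill children. It does not transfer, and the protocol gives no expected frequency of serious events.
- A reader might infer that **causality is always judged with the arm known**. The text leaves the order open. It permits this but does not require it.

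**Conclusion.** The point holds as an internal contradiction. Section 11.6, followed as written, discloses the arm of each reported child to the coordinator and the principal investigator, against 6.2 and 6.3 and outside the exception in 8.6. For non-serious suspected reactions no exception exists at all.

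Its size is the number of reported children, which the documents do not allow one to estimate and which the conclusion does not need. The conclusion rests on reading the field list in 11.6 as applying to every report it describes, and on annex F8 containing no masking that the text fails to mention. It should be corrected because it weakens the trial's only blind at the points where causality is judged and weighing is supervised. It is not evidence that the allocation list as a whole is exposed or that the primary comparison is biased.

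**What to change.** Reconcile sections 6.2, 6.3, 8.6 and 11.6:

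1. In 11.6, remove the study group from the report's contents and identify the child by study number only. Make the same change in annex F8 if the field appears there.
2. State that severity and causality are recorded before any allocation is released.
3. State that the dispenser releases the allocation only under 8.6, or sends it to a person confirmed to be outside the blinded list. The sponsor's medical director sits on the safety subgroup, but 6.2 blinds co-investigators and the text at hand does not show whether that role is one of them. This needs confirming before the role is named.
4. State what applies to non-serious suspected reactions, which 8.6 does not currently cover.

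The cost is one form field and a few sentences. Blinded reviewers would see the arm only when unblinding is judged necessary, and urgent unblinding is unaffected.

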#### **11.7 Interim analysis and Data and Safety Monitoring Board**

An interim analysis is not required in this study. The study sample size and the 6 month follow-up period is the minimum needed before having the statistical power to show evidence of any significant (operational or statistical) difference in the primary outcome (negative nutritional outcome; 'NNO') when comparing study groups.

In addition, occurrence of SAE's, SAR's and mortality will be monitored, evaluated and reported routinely throughout the study. A subgroup of the study advisory group (including the OCBA Medical Director, the Primary Investigator and Field Research Coordinator) will continuously review the occurrence of all SAEs and SARs. On authority of the OCBA Medical Director or the MoH of Kaabong, the study can be interrupted, altered or stopped as a result of these investigations. The MSF ERB and local ERB/MoH will be immediately informed if this is the case.

Due to the proven safety of the supplementation products and because the products are not used in a manner very different than that already proven safe, the use of an independent Data and Safety Monitoring Board (DSMB) is not warranted. If the advisory committee is unable to make a decision on the outcome of the interim analysis, an independent body external to MSF will be immediately consulted.

**Authorship**

The PI is responsible for drafting the report of this study, in collaboration with the OCBA and OCA epidemiologist or investigator. Publication in an appropriate medical scientific journal will be sought. The PI is responsible for ensuring the collaboration and consent of all co-workers and for submitting a draft version of the final report to the advisory committee within three months of completion of the study.

Authors will be drawn from the advisory committee and will be considered to be authors on 1) substantial contributions to conception and design, acquisition of data, or analysis and interpretation of data; 2) drafting the article or revising it critically for important intellectual content; and 3) final approval of the version to be published. Authors should meet conditions 1, 2, and 3.

Other members of the study group will be acknowledged as contributors in any publications or presentations.

-----

